### Recruitment

Recruitment will take place over a period of 12 months. Individuals will be identified as potential participants on a consecutive basis from the waiting list of Sight Cymru, having previously been referred to this service. Those who are interested in the study will be screened for eligibility. If eligible, potential recruits will be sent a written information sheet.

It is expected that up to 15 % of participants may be lost to follow-up. In order to minimise attrition, participants will be carefully informed at recruitment of the study requirements, the importance of completion of the study and the value of their contribution.

### Inclusion criteria

Individuals over the age of 18 years who require Visual Rehabilitation Officer input will be included. The Sight Cymru criteria for service provision includes anyone with sight loss that cannot be corrected by glasses and that causes them significant difficulties in carrying out daily tasks, regardless of blind or partial sight registration status.

### Exclusion criteria

To maximise the generalisability of the results, the exclusion criteria will be kept to a minimum. Exclusion criteria include ineligibility for the ROI (those aged < 18 years or living outside of geographical catchment area) or those who have significant need, for example significant risk of injury at home (it would be unethical to randomise those at risk of injury to a 6-month waiting list). These individuals will be moved to a fast-track service. Previous recipients of a comprehensive visual rehabilitation service, since their most recent significant decrease in vision, will not be included. Participants who screen positive for significant cognitive or memory problems according to a shortened version of the Mini-Mental State Exam (MMSE) will be excluded. Participants will not be included if they are unable to use a telephone (for example, caused by very poor hearing, unable to understand English, unable to take part in a 6-month study, and unable to provide informed consent). Individuals with planned cataract extraction over the next 6 months will also be excluded.

### Study procedures: consent, baseline assessments, randomisation and interviews

After receiving the study information sheet, participants will be contacted by the interviewer and invited to attend a baseline visit at the School of Optometry and Vision Sciences. At the baseline visit, further screening for the study criteria will take place. Informed consent will then be collected, in addition to a medical history. Visual acuities (EDTRS) and contrast sensitivity (Pelli-Robson) will be measured. Confidentiality of personal information will be maintained by the interviewer, who will anonymise all data.

The baseline telephone interview will take place within one week of the baseline visit. At the baseline telephone interview, the masked interviewer will explain that the interview results are confidential, prior to performing the baseline questionnaires. Within 1 week of the baseline interview, the participants will be randomly assigned (computer-generated schedule) by site staff, to receive the Visual Rehabilitation Officer intervention or to remain on the Sight Cymru waiting list (control) in the ratio 1:1. In the randomisation process, participants will be stratified by age (older than or younger than 65 years) and baseline visual acuity (better or worse than 1.0 LogMAR). In order to minimise the risk of predicting the group allocations, randomisation will be performed in permuted blocks of two, with random variation of the blocking number. Those assigned to the intervention group will receive their first appointment with the Visual Rehabilitation Officer within 3 weeks (±1 week) of randomisation. All data collection will be conducted by one interviewer, masked to the group allocations. Participants will be reminded not to reveal their group allocation to the interviewer during any mutual communications. All participants will have access to hospital- and community-based low vision optometric assessments; that is, the control and intervention groups will differ only in the receipt of the Visual Rehabilitation Officer visits to the intervention group.

Six months after the baseline telephone interview, a follow-up telephone interview will be conducted by the interviewer. In addition to the follow-up questionnaires, information about any change in circumstance over the past 6 months will be collected, such as a change in eye condition status, change in life events or living situation, change in general health or treatments, or referral to other community support services. After the questionnaire outcomes have been collected, the interviewer will be unmasked by opening a sealed envelope, containing the group allocation for each participant. The interviewer will then assess intervention satisfaction, using items from the Manchester Low Vision Questionnaire [37], a validated questionnaire, consisting of a question about how helpful participants perceive the intervention to be, with five response categories. In addition, the interviewer will pose two open questions asking about aspects of the service with which the participants were satisfied or dissatisfied.

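### Blocks of two, combined with unmasking the only interviewer during the trial, let that interviewer infer the arm of participants whose outcomes are still to be collected

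*Protocol article*

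**What the plan says.** All of the following is in the protocol article, under the study procedures heading unless another section is named.

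- **Blocking.** "In order to minimise the risk of predicting the group allocations", the plan says, "randomisation will be performed in permuted blocks of two, with random variation of the blocking number". The ratio is 1:1, and "participants will be stratified by age (older than or younger than 65 years) and baseline visual acuity (better or worse than 1.0 LogMAR"), which makes four strata.
- **Timing of randomisation.** "Within 1 week of the baseline interview, the participants will be randomly assigned (computer-generated schedule) by site staff".
- **Assessor.** "All data collection will be conducted by one interviewer, masked to the group allocations".
- **Unmasking.** "After the questionnaire outcomes have been collected, the interviewer will be unmasked by opening a sealed envelope, containing the group allocation for each participant". The same interviewer then asks the satisfaction items.
- **Calendar.** Follow-up falls six months after each participant's own baseline interview, with a window of one month either side (Outcome measures). Recruitment lasts 12 months (Recruitment) and the trial 18 months (opening of Methods/design).
- **Masking check.** Masking violations are recorded, and the interviewer guesses the allocation before the final follow-up (Outcome measures).

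Nothing in the article says that the interviewer stays masked until every participant's outcomes are in.

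**The concern.** Two instructions work against each other. The block size is presented as protection against prediction, yet in a block of two at 1:1, knowing one allocation fixes the other. The person who must not know the allocations is then handed them during follow-up.

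The interviewer also has what is needed to link participants. Randomisation follows the interviewer's own baseline call within a week, so the order of entry is roughly known. Collecting all data would include the age and acuity that define the strata.

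The primary and secondary outcomes are self-reports taken by telephone by this one person, and participants know their own arm. Masking the interviewer is therefore the main remaining protection against bias from how the call is conducted and scored. The trial's declared product is robust effect estimates for planning a definitive trial, and a bias here would carry into that design.

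**Working it through.** The article gives no figure for predictability, so there is none to reproduce.

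**Step 1: timing.** Recruitment runs over months 0 to 12. Follow-up comes 6 months (±1) after each baseline interview, so outcome calls run from about month 5 or 6 to month 18. If envelopes are opened call by call, the first are opened while most participants still await follow-up. The ±1 month window does not help: whichever member of a pair is opened first reveals the other.

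**Step 2: block size fixed at two.** Assume that the interviewer can pair participants correctly.
- Share certain: the second of each pair, 1/2 = 50%.
- Share guessed correctly: (0.5 + 1)/2 = 75%, against 50% by chance.
- With 70 participants in four strata, some strata have an odd count. Simulation gives 33 to 35 complete pairs, mean 34. That is 34/70 = 49% certain and (34 + 36 × 0.5)/70 = 74% guessed correctly.

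**Step 3: attrition.** An envelope is opened only after a completed follow-up, and the plan expects about 15% loss. If losses are independent, both members of a pair are followed up with probability 0.85² = 0.7225. Then 35 × 0.7225 ≈ 25 interviews are exposed, out of 70 × 0.85 ≈ 60 completed.

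**Step 4: block sizes varied and undisclosed.** The article does not give the sizes, so these are assumptions. For an equal mix of 2 and 4, once a block's first allocation is seen, the next is in the opposite arm with probability 1/2 × 1 + 1/2 × 2/3 = 5/6 (83%), provided that the start of the block is known. The table comes from simulating 70 participants in four strata. The guesser knows the stratum, the order, the permitted sizes and all earlier allocations in the stratum, but not the block boundaries. Three assumed stratum mixes gave nearly the same results.

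| Block sizes | Certain | Predictable at 80% or better | Guessed correctly |
|---|---|---|---|
| 2 | 49% | 49% | 74% |
| 2, 4 | 10% | 54% | 71% |
| 2, 4, 6 | 3–4% | 46–47% | 69% |
| 4, 6 | 5–6% | 28–30% | 68% |
| 4, 6, 8 | 2% | 20–21% | 67% |

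In long sequences, without incomplete last blocks, the 2/4 mix rises slightly, to about 55% predictable at 80% or better and about 72% guessed correctly.

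**Step 5: the undefined phrase.** If the variation concerns only which of the two orders a block of two takes, every block still holds one participant per arm and Step 2 applies in full. If it concerns block size, Step 4 applies.

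**The case against.** The strongest defence is that the size of the leak depends on two ambiguous phrases in a condensed article. Block sizes and concealment details commonly sit in the full protocol. Several stronger readings are tempting, and the document does not support them.

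- **That the interviewer will know half the arms for certain.** This needs a fixed size of two, knowledge of the scheme and correct pairing. The article mentions random variation, and the interviewer knows the order of randomisation only to within about a week. With varied, hidden sizes, deduction becomes guessing better than chance.
- **That 39% would be certain under a 2/4 mix, or 28% under 4/6.** Those figures come from (1 + 4/3)/6 and (4/3 + 3/2)/10, which count forced allocations for someone who also knows where each block begins and ends. With boundaries hidden they are about 10% and 6%.
- **That 35 interviews are exposed.** This ignores the plan's own expected attrition.
- **That one-at-a-time opening, or the interviewer running the baseline visit, is stated.** Both are inferences. The envelope sentence could describe one envelope listing everyone, which is harmless if opened after the last outcome call and worse if opened earlier. The baseline visit is described without naming who conducts it.
- **That site staff could use the predictability to select participants.** Identification is consecutive from a waiting list, and consent and baseline questionnaires precede randomisation, so no clear harm follows.

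Two further points are fair. Much reporting bias would remain whatever the interviewer knows, because participants know their arm. The trial is also exploratory and will be interpreted through descriptive statistics and confidence intervals. Both lower the severity. The recorded guess is a real safeguard, but it can only detect a leak, not prevent one.

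What stands is that the block size works against its stated purpose, and nothing in the article stops the sole assessor from learning allocations before all outcomes are collected.

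**Conclusion.** The point holds and should be fixed. With block size fixed at two and participants correctly paired, up to half of allocations are deducible and 75% guessable. That is about 25 of 60 completed interviews under independent 15% loss, and it is an upper value. With undisclosed sizes of 2 and 4 (assumed), about 10% are certain, about 55% predictable at 80% or better, and about 72% guessed correctly. Masking is weakened on either reading.

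The conclusion rests on participant-by-participant unmasking, which is the natural reading of the timetable but is not stated outright. It also rests on the interviewer knowing the blocking scheme, each participant's stratum and the approximate order of entry. A reader might infer that assessor masking fails altogether or that the estimates will be biased by a known amount. The document supports neither: it shows an avoidable route for bias, not that bias occurred or how large it would be.

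**What to change.** 1. **Essential.** State that the interviewer receives no allocation until the last 6-month outcome questionnaire of the whole trial is complete. The satisfaction items can be asked by existing staff who already know the allocation, or by the interviewer after that point. This closes the envelope leak whatever the block size.
2. **In addition.** For the remaining allocations, drop blocks of two and use larger, randomly varying blocks within strata, for example 4 and 6, with sizes not disclosed to the interviewer or enrolling staff. On its own this reduces predictability (about 68% guessed correctly for 4/6, against 71–72% for 2/4 and 74–75% for fixed two) but does not remove it. Also say what the random variation refers to.

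The cost is a procedural note, a new list for participants not yet randomised (recruitment was under way at submission), a short separate or later contact for the satisfaction items, and slightly more possible imbalance within the four strata.

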### Analysis

All data will be entered into the Statistical Package for the Social Sciences Ver. 20.0.0.2 (SPSS Inc., Chicago, IL, USA) and recoded such that all items have a consistent valance (that is, all items are valanced positively). Any missing data will be recorded, along with any protocol violations.

The VA LV VFQ-48 baseline data will be analysed with Rasch analysis according to the Andrich Rating Scale model using Winsteps ver. 3.75.0 [38]. Rasch analysis is a probabilistic logistic model, which produces Logit values describing item difficulty and person ability, providing questionnaire scores which are on a true interval scale. A scoring key will be produced allowing conversion of the raw questionnaire scores into an interval level score. Rasch analysis will also be used to confirm instrument unidimensionality and assess reliability of item measures.

Of the secondary outcome measures, the WEMWBS and AVL-12 will be Rasch analysed using the same method as described above in order to obtain item measures, confirm unidimensionality and reliability of items. The remaining secondary outcome measures (PHQ-9, EQ-5D and UCLA scale) will be analysed using standard scoring, for comparable results to previous studies using these measures.

Demographic data will be reported using summary statistics. In order to demonstrate study feasibility, an assessment of participant eligibility, recruitment, retention to follow-up, missing data, adherence to the intervention and acceptability of the intervention will be reported by descriptive data. Successful adherence to the intervention will be defined as completed visits by the Visual Rehabilitation Officer.

Baseline characteristics will be summarised by descriptive statistics. Questionnaire scores at follow-up will be analysed using analysis of covariance (ANCOVA), controlling for the baseline score and the key variables (age, co-morbidities and visual acuity) as covariates. A logistic regression analysis will investigate whether the number of intervention items is associated with the outcomes. Standard diagnostics will be used to check model fit (for example, residual versus fitted plots), and standard transformations (square root, log and square) explored where necessary. The analysis will be complete case and intention to treat. This exploratory study is not powered to identify statistically significant differences; therefore, the results will be interpreted using descriptive statistics and 95 % confidence intervals.

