Communication• Potential difficulties with telephones, appointments, correspondence, finance management, IT.	Support and advice on the following:• Appropriate telephones and related devices.• Telephone banking, telephone/online shopping.• Note taking and maintaining appointments diary (large print, address guides).• Techniques or equipment suitable to needs for reading, general correspondence, telling the time.• Strategy for accessing bank and money management• Computer technology assistance and referral for IT skills training.

There is evidence that impaired functional status in individuals with visual loss is associated with depression [7–9], psychosocial impact [10–12], risk of falls, decreased mobility [13–15] and higher rates of mental and physical health comorbidities. Partial evidence exists of improved health-related quality-of-life outcomes following visual rehabilitation intervention [16, 17] and improvement in vision-related quality-of-life following visual rehabilitation [16, 18–20]. However, a paucity of high-quality evidence exists regarding the effectiveness of low vision rehabilitation services, particularly with regard to social care provision [6].

The need for evidence to support the low vision rehabilitation service is driven by the necessity to inform direction for healthcare resources, as a result of the growing social and economic challenges faced by those with visual impairment [6]. The burden on such resources is growing with the increase in the elderly population and therefore, the increasing number of individuals with low vision. The evidence gained from this study will inform the design of a definitive trial, which will help shape the development of low vision rehabilitation services in the UK.

The primary aim is to examine the effect of a Visual Rehabilitation Officer intervention (ROI) on self-reported visual function. The secondary aims are to determine the effect of the low vision rehabilitation service on depression, well-being, loneliness, adjustment to visual loss and generic health-related quality-of-life. The relation between the numbers of intervention items received on the outcomes will also be assessed.

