### Intervention

There is one active intervention in the trial, that is, the ROI. In one to eight sessions, a Visual Rehabilitation Officer will conduct home visits to assess the status of the individual with low vision and provide training and support in specific areas of need.

The support is tailored to the individual in a number of areas including mobility, use of low vision aids, household tasks, communication and administrative tasks. Table 1 details the types of intervention that may be provided by the Visual Rehabilitation Officer. Not all components are provided to each person, because the ROI is tailored to meet individual requirements (Table 1). The aim of the rehabilitation is to promote independence by helping individuals learn new skills or regain lost skills and rebuild confidence following sight loss. This support may be implemented by the provision of information, equipment, encouragement, training and/or referral to other agencies. This type of intervention is typical of that provided by Visual Rehabilitation Officers in the UK.

For each participant in the intervention arm, a list of intervention items implemented and the number of visits will be recorded, by the Visual Rehabilitation Officer (Table 2). In this trial, participants will be recruited from South East Wales. The intervention will be provided by a team of two experienced Visual Rehabilitation Officers (each with 7 to 8 years of experience) based at the Sight Cymru rehabilitation service. This service was chosen for its proximity to the research centre at Cardiff University and the willingness of the service to support a rigorous research study.

**Table 2 Tab2:** List of intervention items recorded by the Visual Rehabilitation Officer

Intervention items:
Initial assessment
Functional vision assessment
Low vision training/advice
Magnification advice
Lighting advice
Personal care/medication advice
Washing and dressing
Medication management
Kitchen skills
Safe pouring technique
Food preparation/cooking
Cleaning/managing the home
Laundry
Ironing
Money issues
Orientation and mobility training
Road safety check
Sighted guide technique
Symbol cane advice
Guide cane training
Long cane training
Communications
Reading and writing
Accessing TV and radio
Using phones
Telling the time
Audio books
IT
Social and leisure activities
Emotional well-being
Referrals to other agencies (specified)
Other (specified)

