### Outcome measures

Outcome measures will consist of the questionnaires administered at baseline and 6 months (±1 month) follow-up. The primary outcome measure will be the 48-item Veterans Affairs Low Vision Visual Functioning Questionnaire (VA LV VFQ-48), a validated unidimensional functional outcome measure questionnaire that assesses the difficulty in performing daily activities in visually impaired individuals [21]. Secondary outcome measures will include: the Patient Health Questionnaire (PHQ-9), an assessment of depression symptom severity on a nine-item scale, based on criteria for depressive episodes including concentration problems and suicide [22]; the Warwick-Edinburgh Mental Well-being Scale (WEMWBS), a population measure of subjective well-being, involving 14 positively worded questions about aspects of positive thoughts and feelings [23]; the Adjustment to Age-related Visual Loss Scale (AVL-12), a measure of psychological adjustment to vision loss [24]; the standardised Health-related Quality of Life Questionnaire (EQ-5D), a ‘utility’ measure to assess five health-related dimensions, that is, mobility, self-care, usual activities, pain/discomfort and anxiety/depression [25]; and the UCLA Loneliness Scale, a 20-item scale to measure subjective feelings of loneliness and social isolation [26].

These instruments were selected on the basis of the following evidence. The VA LV VFQ-48 has been assessed as a high-quality instrument for use in evaluating adults with low vision [27]. The PHQ-9 is a suitable measure of depressive symptoms in those with visual loss [28]. Mental well-being is a prominent issue in governmental health policy, and the utility of the WEMWBS has been demonstrated in general populations [29]. The AVL-12 has been adopted effectively in several trials of individuals with low vision following rehabilitation [30–32]. Whilst the EQ-5D may be unresponsive to low vision rehabilitation [33], it is the preferred measure of health utility by the National Institute of Clinical Excellence guidance (NICE article PMG9, 2013). It is acknowledged that health disorders are risk factors for loneliness [34], and the UCLA scale has been used to evaluate individuals with low vision [35].

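### Logistic regression is named for relating the number of intervention items to outcomes that are all questionnaire scores with no event defined, and the item count is driven by need

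*Protocol article*

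**What the plan says.** The last paragraph of the Background gives the primary and secondary aims and then adds a further question: "The relation between the numbers of intervention items received on the outcomes will also be assessed". The model for it is in the Analysis section: "A logistic regression analysis will investigate whether the number of intervention items is associated with the outcomes". That sentence gives no event, covariates or analysis population.

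The outcomes are set out under Outcome measures: "Outcome measures will consist of the questionnaires administered at baseline and 6 months (±1 month) follow-up". They are the VA LV VFQ-48 (primary), PHQ-9, WEMWBS, AVL-12, EQ-5D and UCLA Loneliness Scale. The Analysis section applies Rasch analysis to the VFQ-48, WEMWBS and AVL-12, describing the method as "providing questionnaire scores which are on a true interval scale". For the others: "The remaining secondary outcome measures (PHQ-9, EQ-5D and UCLA scale) will be analysed using standard scoring".

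The group comparison treats the same scores as continuous: "Questionnaire scores at follow-up will be analysed using analysis of covariance (ANCOVA), controlling for the baseline score and the key variables", namely age, co-morbidities and visual acuity. The sentence after the logistic one reads "Standard diagnostics will be used to check model fit (for example, residual versus fitted plots", and goes on to square-root, log and square transformations.

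On how items are given, the Intervention section says "Not all components are provided to each person, because the ROI is tailored to meet individual requirements". It has the Visual Rehabilitation Officer record items and visits for intervention-arm participants only.

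**The concern.** There are two separate problems.

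The first is the model. A binary logistic regression needs an event. The article defines none for any of the six scales, so someone following the text would have to choose up to six cut-points, possibly after seeing the data. Splitting a score also discards information, and there are only about 30 people in whom the question can be asked.

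The second is the exposure. The number of items is not a randomised dose. People with more difficulties can be expected to receive more items and also to score worse at follow-up. Without adjustment, a helpful intervention could look weaker than it is, or even harmful. The Discussion says the trial's estimates will be used to design a larger trial, so a misleading relation between items and outcome could influence how intensive that intervention is made.

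**Working it through.** **Does the named model fit the outcomes?**

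| Outcome | Scoring in the Analysis section | Event or category defined? |
|---|---|---|
| VFQ-48, WEMWBS, AVL-12 | Rasch interval measure | No |
| PHQ-9, EQ-5D, UCLA | Standard score | No |

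The only categorical participant response is the five-category helpfulness item under Study procedures. It is not among the listed outcome measures, and it is not binary. A binary logistic fit to a continuous score is rejected by the software, because the response must lie between 0 and 1. The group-comparison sentence just before uses ANCOVA. The diagnostics and transformations just after belong to linear models, although they may be meant for the ANCOVA alone, so they support the point without deciding it.

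**Cost of a median split (illustration).** The input from the article is n = 30 in the intervention arm at follow-up (Sample size). The slopes are assumptions, in standardised units, with no confounding; 1,500 simulated data sets each.

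| Assumed slope | Power, linear | Power, median-split logistic |
|---|---|---|
| 0.4 | 61% | 37% |
| 0.2 | 21% | 11% |

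The article does not specify a median split. This shows the cost of one natural choice.

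**Bias from need (illustration).** All inputs except n = 30 are assumptions. Need has mean 0 and SD 1, and its correlation with item count is ρ. The baseline score is −0.5 × need plus noise. The follow-up score is 0.5 × baseline + 0.2 × items − g × need plus noise. The true item slope is therefore +0.2.

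Expected slope without adjustment: 0.2 − ρ(0.25 + g), where 0.25 = 0.5 × 0.5.

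Expected slope adjusted for baseline score: 0.2 − g × 0.75ρ / (1 − 0.25ρ²).

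- Mild (ρ = 0.3, g = 0.2): unadjusted 0.2 − 0.3 × 0.45 = +0.065; adjusted 0.2 − 0.2 × 0.225/0.9775 = +0.15.
- Moderate (ρ = 0.5, g = 0.5): unadjusted 0.2 − 0.5 × 0.75 = −0.175; adjusted 0.2 − 0.5 × 0.375/0.9375 = 0.00.
- Strong (ρ = 0.7, g = 0.5): unadjusted 0.2 − 0.7 × 0.75 = −0.325; adjusted 0.2 − 0.5 × 0.525/0.8775 = −0.10.

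Simulation at n = 30 agrees:

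| Case | Mean unadjusted slope | Unadjusted slope negative | Mean slope adjusted for baseline |
|---|---|---|---|
| Mild | +0.07 | 38% of runs | +0.16 |
| Moderate | −0.17 | 81% of runs | +0.01 |
| Strong | −0.33 | 95% of runs | −0.10 |

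The median-split logistic slope was negative in 38%, 75% and 90% of runs. The bias is downward in every case, but the average sign changes only in the moderate and strong cases. Adjusting for baseline score moves the estimate towards the truth without fully correcting it, because in this set-up need is more than the baseline score.

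**The case against.** The strongest reply is that this is one sentence about an exploratory question in a condensed article. Cut-offs, covariates and analysis population are commonly left to a full protocol or analysis plan, which is not shown. Silence about adjustment is not a commitment to an unadjusted analysis. An ordinal logistic model can be fitted to summed scores, so it is too strong to say that logistic regression always needs a binary outcome. The article also says it will rely on descriptive statistics and confidence intervals, not significance tests.

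Much of this stands. The missing covariates alone would not be a finding. But the article does name a model, and that model does not match the outcomes it defines. It mentions no ordinal model, and one would sit oddly beside the effort to obtain interval scores. Relying on intervals does not help either, since bias moves the estimate and its interval together.

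Three stronger readings are tempting but not supported:

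- **That the answer will be reversed.** Reversal needs moderate or strong confounding by need, and the article gives nothing from which to judge its strength. Calculated false-positive rates are equally dependent on assumptions. With no true item effect, they are about 35% to 63% if items rise 28% per SD of worse baseline, but below 10% if they rise 5%.
- **That controls will be entered with zero items.** This would make the count largely a proxy for arm, but no text proposes it.
- **That the count double-counts headings and their components in Table 2.** The table is available here only as flattened text, and the article does not say that headings are counted.

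**Conclusion.** The point holds as a misstated method. Logistic regression does not suit the outcomes as defined, and no event is given that would make it suit them. Because items are tailored, an unadjusted association would be biased by need, in the direction of understating benefit if greater need goes with worse follow-up scores. Sign reversal is possible but not established. The power loss (61% to 37%) and the slope shifts (from +0.2 to between +0.07 and −0.33) rest on assumed inputs and show the range, not a prediction.

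A reader might infer that a stated secondary aim or the main result is compromised. Neither follows: the item-count question is added after the secondary aims, and the randomised ANCOVA comparison does not use it. Severity is minor to moderate.

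**What to change.** Replace the logistic sentence with one along these lines: within the intervention arm, the follow-up score on each scale will be regressed linearly on the number of intervention items received, adjusting for the baseline score, age, co-morbidities and visual acuity; the slope will be reported with its 95% CI as a non-randomised association in which residual confounding by need remains.

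The covariates are those already named for the ANCOVA. If each enters as a single term, the model has six coefficients including the intercept, leaving 30 − 6 = 24 residual degrees of freedom, which is workable for a descriptive slope. The caveat about residual confounding should stay, because adjusting for baseline score may remove only part of the bias.

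If logistic regression is truly intended, state for each outcome the event and its cut-off before follow-up data are examined, with the same restriction, adjustment and caveat.

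The cost is one or two sentences, with no new data and no change to the sample size or the main analysis.
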